## Methods/design

### Trial design

This study uses a two-arm pilot randomized Hybrid Type 3 design [14]. Four Family Spirit home visiting sites from the Inter-Tribal Council of Michigan (ITC of MI) were selected based on comparability and randomized using a 1:1 allocation to provide either Standard Family Spirit or Precision Family Spirit to their clients. Sites were matched based on annual volume of clients served and geographic similarity (i.e., urban vs. rural) (Fig. 1).

**Fig. 1 Fig1:**
[figure not shown]
Study design and data collection

### Participants

Our target population for recruitment is women who are *either* pregnant or have a baby no older than 2 months of age. All study participants must be at least 14 years of age and already enrolled in the Family Spirit program in their community. Since 2013, the CAIH and the ITC of MI have partnered on implementing the Family Spirit model across participating tribal communities. The ITC of MI has a strong infrastructure to support the incorporation of a research study into their existing home visiting programming.

### Participating communities

Four ITC of MI sites are participating in this pilot trial, all located in the US and primarily serving Native American families—two in the Upper Peninsula of Michigan (MI) and two in the Lower Peninsula of MI, one of which is an Urban Indian Organization (UIO). The ITC of MI was founded in 1968 to combine efforts of a few Native American tribal communities. Working collaboratively allowed these tribal communities to leverage resources and expand programs to enhance the health and well-being of tribal members. Today, the ITC of MI is a consortium of all 12 federally recognized tribes and 1 UIO in Michigan. Member tribes directly manage local program operations while ITC of MI provides technical assistance and administrative support, often serving as grantee on projects involving a consortium of tribes. To respect tribal sovereignty and their wishes, the participating Tribes’ names have been left out of this paper.

Native American communities in the Upper Peninsula are rural and geographically isolated. While a sizeable portion of the population lives on reservation land in relative proximity to tribal services, many live off reservation across a wide area of multiple counties. Historical trauma and government policies which disrupted tribal communities’ economic, social, and cultural structures and overall way of life have led to disparities across income, employment, health, and wellness compared to the Michigan general population. Likewise, Lower Peninsula tribal communities face socioeconomic and health disparities as a result of historical trauma and government policies. While Lower Peninsula communities are characterized as more semi-urban and urban as compared to those in the Upper Peninsula, their families are facing similar challenges. Thus, both Lower and Upper Peninsula communities have been using home visiting as a part of a larger strategy to strengthen families.

### Family Spirit Model

The Family Spirit evidence-based home visiting model was designed and tested by the CAIH in partnership with tribal communities over a 20-year period [10]. It is currently the largest, most rigorous, and only evidence-based home visiting program designed for pregnant and parenting Native American families. Family Spirit trains Native American community members to serve as home visitors who provide structured, culturally grounded education to families with children ages 0 to 3. The goal is to produce healthier pregnancies and healthier future generations by providing education around pregnancy, parenting, child development, and life skills and connecting families with community resources. The model was designed for delivery by paraprofessionals but can also be delivered by professionals. The employment of paraprofessionals to deliver the program is more sustainable and builds capacity within communities that suffer low employment and poor access to health care and education. It also allows for cultural match between home visitors and participants, as most professionals in the communities are non-Native.

Family Spirit utilizes a 63-lesson curriculum, which was designed through a community-based participatory process led by the CAIH in partnership with three Southwestern Native American tribal communities. The original curriculum was evaluated through three successive randomized controlled trials (RCTs), each one increasing in length and rigor and corroborating prior findings. In the third and largest RCT, all families in the intervention study arm received all Family Spirit lessons. Lesson visits typically lasted an hour and started out weekly and decreased in frequency over time, until they were being taught bimonthly from 2 to 3 years postpartum. Family Spirit has demonstrated the following impacts: increases in parenting knowledge [10–12, 15] and self-efficacy [10, 15]; reductions in parenting stress [12, 15] and maternal psychosocial risks that could impede positive parenting, including substance use [15] and depression [11, 12, 15]; and improved children’s social, emotional, and behavioral development [10, 12, 15]. Based on these findings, in 2013, Family Spirit received the highest ratings for an “evidence-based” program from the federal HomVEE review of home visiting program effectiveness and a 4.0 out of 4.0 for dissemination readiness from the National Registry for Evidence-Based Practices and Programs (NREPP). At present, over 130 tribal communities and 4 urban non-Native communities across 22 US states have been trained to deliver Family Spirit*.* The program has been adopted by non-Native communities due to its unique cultural strengths, use of paraprofessionals, and strong evidence of effectiveness. Family Spirit respects tribal data sovereignty and thus does not report nationally on retention of participating families. However, like other home visiting models being disseminated across the US, Family Spirit affiliates have shared challenges with retention and engagement of families for the duration of the program. A precision approach to Family Spirit provides promise to addressing this issue of implementation of an evidence-based home visiting program at scale.

### Recruitment

The pilot study is recruiting *N* = 60 women who meet the inclusion and exclusion criteria below:

### Inclusion criteria

Women who are *either* pregnant or have a baby no older than 2 months oldAt least 14 years of age at time of conceptionEnrolled in Family Spirit services in the participating community

### Exclusion criteria

Inability to participate in full intervention or evaluation (e.g., planned move, scheduling conflicts, etc.)

Ambiguous cases based on unclear age at conception or unclear gestational age are reviewed by the Study Management Team before being deemed eligible for recruitment. Home visitors conduct informed consent procedures with all eligible participants. All participants must provide informed consent or assent to participate. Participants under age 18 must have parent/guardian consent. The first participant gave consent on June 25, 2019, and the first baseline assessment was completed on June 26, 2019.

### Randomization

Participating ITC of MI sites were randomized to use the Precision Family Spirit implementation strategy or Standard Family Spirit (control condition). Randomization occurred before recruitment began at the site level. The four sites were selected based on comparability of annual volume of clients served and geographic similarity (i.e., urban vs. rural). Once sites were matched, the study team flipped a coin to decide which sites would be assigned to each study arm. Participants are blind to whether they receive Standard Family Spirit or Precision Family Spirit as randomization occurs at the site-level. Thus, all participants at each site receive the same version of Family Spirit (standard or precision).

### Ethical considerations

This study was reviewed and approved by the Johns Hopkins Bloomberg School of Public Health Institutional Review Board (JHBSPH IRB) (IRB00009315; Current protocol version: #9, approved on September 8, 2020). Any protocol modifications are submitted as an amendment to the JHBSPH IRB. Supervisors then inform study staff and conduct additional trainings as needed. If protocol modifications are significant, trial registries are updated.

Serious adverse events (e.g., participant death or hospitalization) for both mothers and/or children are reported on a real-time basis to the JHBSPH IRB. All study investigators have been trained and certified in basic human subject research, HIPAA compliance, and Social and Behavioral Research Best Practices for Clinical Research. All home visitors have also been trained and certified in HIPAA compliance.

### Standard Family Spirit

Mothers at the control sites receive Family Spirit as usual, per existing ITC of MI program policies and procedures. In the standard of care, families receive regular home visits, delivered in the same sequence until 3 years postpartum (63 lessons total). Because the duration of enrollment for this pilot study is from pregnancy to 12 months postpartum, Standard Family Spirit participants should receive 47 lessons total. Home visitors at Standard Family Spirit sites use the Care4 platform to track their clients. They receive notifications about high depression scores, risk of self-harm, and potential domestic violence issues, but they do not receive notifications about other risk categories (first-time mom, substance use, nutrition, sexual and reproductive health) that would inform tailoring sequences in the Precision Family Spirit implementation approach. Details on the rationale for selecting these risk categories have been described elsewhere [9, 16].

In both arms of the study, home visitors provide referrals and connections to community agencies and services as needed. Existing procedures are in place to link participants to assistance that is available in their area. Home visitors often act as navigators and advocates for the families they serve. In addition, participant transportation to and from doctor and clinic appointments is common and will continue for enrolled participants in each arm.

The study team recognizes that differences may be small regarding number of prescribed lessons between Precision Family Spirit and Standard Family Spirit participants, but implementation outcomes may be potentially detectable because we are measuring program participant acceptability, satisfaction, quality of relationship between home visitor and client, retention, and adherence.

### Implementation strategy: Precision Family Spirit

Our selection of an implementation strategy is guided by the Proctor et al. 2009 conceptual model of implementation [17]. Home visiting models in practice struggle with low retention rates [3]. Thus, we used design modularity as an implementation strategy that would improve engagement and retention. The specification of our implementation strategy can be found in Table 1 [18].

**Table 1 Tab1:** Specification of Family Spirit implementation strategy

Domain	Strategy: modularization of an EBT
Actor(s)	Program development team; Implementers
Action(s)	Generate appropriate lesson pathways; implement these using an electronic support platform (Care4)
Target(s) of the action	Home visitors implementing Family Spirit; Clients receiving Family Spirit
Temporality	During the entire delivery of the program
Dose	Continuous
Implementation outcomes affected	Penetration (engagement and retention) among eligible clients; Adherence to the active prescribed ingredients of Family Spirit
Justification	Research suggests that retention is low in home visiting programs and tailoring of the program improves engagement and retention.

*Note:* Guidelines for specification of the *Family Spirit* implementation strategy from Proctor et al. (2013)

This modularized approach to Family Spirit is called Precision Family Spirit. Precision Family Spirit was developed using mixed methods, including a secondary data analysis to identify meaningful subgroups that could inform how and when to tailor, and stakeholder workshops with program implementers (supervisors and home visitors) to identify core lessons, and lessons relevant to certain subgroups of clients [9, 16]. It consists of five lesson “pathways” that have been identified through formative work across Family Spirit’s national network of stakeholders [9]. There is a core set of lessons that every mother receives. For this pilot study, that means all Precision Family Spirit participants should receive 25 lessons from pregnancy to 12 months postpartum (the duration of enrollment). She receives additional lessons based on her emergent needs identified through data collection at home visits and at each assessment timepoint (Additional file 1). Thus, a Precision Family Spirit participant could be scheduled to receive between 25 and 41 lessons from pregnancy to 12 months postpartum. For example, if a participant is a first-time mother, she (and her family) will receive 6 additional baby care lessons (covering basic topics such as diapering and how to dress a baby) that are included in the Standard Family Spirit curriculum but may not be relevant for experienced mothers with previous children.

The study uses the Care4 implementation platform, which is a secure, HIPAA-compliant web-based application designed to capture data for the purposes of program implementation and evaluation [19]. Care4 is configured to notify home visitors when a participant needs to be added to any additional lesson pathways. Precision Family Spirit participants are assessed at each lesson visit using a measurement-based care approach [20–22] to understand and respond to emergent needs and help home visitors better track how their clients are doing over time. These short assessments are estimated to take 1–2 min to complete at each visit. Lessons are delivered in the same format as Standard Family Spirit, by trained home visitors in the home of the participant or a private place of their choosing.

### Data collection time points

Participant assessments include maternal self-reports using Care4 and an interview (Table 2). Self-reports are conducted in participants’ homes, another private location, or via text/email on an as needed basis. Data is recorded on either a tablet, computer, or paper. If data is collected on paper, the home visitor enters the data into Care4 upon her return to the office. In some cases, assessments are conducted via text or email, once the home visitor discusses on a case by case basis with the study management team. For example, if a home visit is cut short, assessments may be completed post-visit by the participant. A secure link is sent via text or email with instructions on how to complete and submit. All participants will be assessed at four timepoints: baseline, 2 months, 6 months, and 12 months postpartum. Each assessment timepoint is estimated to take participants between 30 min and 1 h to complete. In an effort to mitigate participant time burden, home visitors complete assessments with participants during already-scheduled visits, by scheduling a separate visit, or by emailing or sending links to participants via SMS to complete the forms on their own time. Precision Family Spirit participants may also be asked to participate in a phone interview at study midpoint (between 4.5 and 6.5 months postpartum) and study endpoint (between 11 and 13 months postpartum), adding an additional 15–20 min of participant time burden for each interview completed. The purpose of these interviews is to further contextualize data being collected as part of the quantitative assessment.

**Table 2 Tab2:** List of hybrid trial objectives and evaluation measures

Pilot trial objectives	Instrument	Timepoint			
		Baseline	2 months postpartum	6 months postpartum	12 months postpartum

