**Secondary objectives**					
Maternal substance use	Alcohol, Smoking and Substance Involvement Screening Test	X	X	X	X
Maternal depression	Edinburgh Postnatal Depression Scale	X	X	X	X
Parenting feeding practices	Child Feeding Assessment		X	X	X
Maternal parental knowledge	Parent Knowledge Assessment	X	X	X	X
Child development	Ages and Stages: Social Emotional - 2*		X	X	X
	Ages and Stages Questionnaire, 3rd Edition*		X	X	X
Quality of life	EURO-QOL	X	X	X	X
Maternal self-efficacy	Parenting Locus of Control			X	X
Maternal stress	Perceived Stress Scale 4	X	X	X	X
Substance abuse/domestic violence risk	Institute for Health and Recovery Integrated Screening Tool	X	X	X	X
Client priority outcomes	Top problems	X	X	X	X

*These measures will not be administered as part of the Care4 data collection platform, as they are licensed by ITC of MI external to the Care4 platform

**Qualitative interviews will only be conducted with intervention participants at midpoint and endpoint

Participants receive a gift card upon completion of the following assessment timepoints: baseline, 2 months, 6 months, and 12 months postpartum. Total possible remuneration for participants in the study is $70 in gift cards.

From study midpoint until the endpoint of the study timeline, home visitors will be asked to participate in focus group discussions (FGDs) by video conference. Each site will participate in up to 10 short FGDs. FGDs will be designed to take approximately 30 min to complete and will be scheduled during regular study site meetings. They will be recorded with permission and transcribed verbatim. Home visitors receive a $15 gift card upon completion of each FGD. Total possible remuneration for home visitors is $150 in gift cards.

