#### Primary outcomes

Our primary outcomes of interest include participant acceptability, satisfaction, quality of relationship between home visitor and client, retention, and adherence. Acceptability is measured from the perspective of the participant using a 15-item scale [16] administered at study midpoint and endpoint. Satisfaction is captured through a 34-item questionnaire used in the Family Spirit trials and adapted specifically for this study and administered at midpoint (around 6 months postpartum) and endpoint. All Precision Family Spirit participants are invited to participate in a short qualitative interview to further explore acceptability and satisfaction using an 11-item interview guide. In addition, we will explore home visitor acceptability and satisfaction through focus group discussions that follow a 9-item interview guide. The quality of the relationship between home visitor and client is captured using the short version of the Working Alliance Inventory (WAI) administered to both participant and home visitor. The WAI measures three domains of the relationship: goal alignment, task alignment, and bond. Retention is measured by comparing the number of participants who drop out in each study arm. Adherence is measured by comparing the percentage of retained participants in each study arm who completed their lessons as prescribed.

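### Acceptability and satisfaction interviews are held only in the Precision arm, in windows that let them come before the 6- and 12-month questionnaires on the same topics

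*Protocol article*

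**What the plan says.** The Table 2 footnote limits the interviews to one arm: "Qualitative interviews will only be conducted with intervention participants at midpoint and endpoint". The Primary outcomes section gives their coverage and subject: "All Precision Family Spirit participants are invited to participate in a short qualitative interview to further explore acceptability and satisfaction". Data collection time points describes them as phone interviews, sets their windows at "study midpoint (between 4.5 and 6.5 months postpartum) and study endpoint (between 11 and 13 months postpartum", and puts their length at "adding an additional 15–20 min of participant time burden for each interview completed".

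Both arms complete questionnaires on the same two constructs. The acceptability form is described as "using a 15-item scale [16] administered at study midpoint and endpoint" and the satisfaction form as "administered at midpoint (around 6 months postpartum) and endpoint". The general schedule reads: "All participants will be assessed at four timepoints: baseline, 2 months, 6 months, and 12 months postpartum". Table 2 lists the questionnaire and the interview under the same primary objectives, in the same 6- and 12-month columns.

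Acceptability and satisfaction are both named as primary outcomes. Primary aim analysis compares their scores between arms in mixed-effects models, using a Precision indicator and its interaction with change over time. The article states no order between interview and questionnaire.

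**The concern.** A conversation about how acceptable and satisfying a programme is may change how a mother then scores it. She may have rehearsed an opinion, or felt attended to, or been prompted to recall particular visits. If both arms had the conversation, the effect would tend to cancel. Here only one arm can have it, and the windows open before the nominal questionnaire times.

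The model cannot separate the two sources. Interview exposure exists only where the Precision indicator equals 1, so any shift it causes enters the coefficient for the strategy. Random effects for individual and site do not help. The pilot is meant to supply estimated effects for a fully powered trial, so a measurement artefact in two of its primary outcomes could be carried into that design.

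**Working it through.** **Order permitted by the schedule**

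| | Midpoint | Endpoint |
|---|---|---|
| Interview window (Precision only) | 4.5–6.5 months | 11–13 months |
| Questionnaires (both arms) | about 6 months | about 12 months |
| Latest interview date | 6.5 months | 13 months |

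At each timepoint the interview window opens before the nominal questionnaire time and closes after it, so either order complies with the plan. In addition, every midpoint interview held within its window (by 6.5 months) comes before the 12-month questionnaire, whichever order is used at 6 months.

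**Where a shift would go**

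Let p6 and p12 be the shares of the Precision arm interviewed before the form at 6 and 12 months. Let s be the average shift caused by an interview just before the form, and c the arm-average carry-over of the midpoint interview to 12 months. For simplicity, c is taken to be the same under either order. With no interviews in the Standard arm, the distortion of the arm comparison is:

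| Quantity | Current windows | Questionnaire first |
|---|---|---|
| 6-month difference | p6·s | 0 |
| 12-month difference | p12·s + c | c |
| Difference in 6-to-12-month change | (p12 − p6)·s + c | c |

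The ordering rule clears the 6-month comparison and removes same-timepoint priming at 12 months. It does not remove c. None of p6, p12, s or c is given in the documents.

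**Scale, by assumption only**

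The plan has no figure of its own to reproduce on this point. Inputs from the sample size section: N = 60, 30% attrition, alpha 0.05. Then 60 × 0.70 = 42, or 21 per arm if the arms are equal. Sidedness is not stated; two-sided is assumed. Clustering by site is ignored and the true difference is set to zero.

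- Standard error in SD units: √(2/21) = 0.309.
- Rejection probability for an arm-level shift b: Φ(−1.96 + b/0.309) + Φ(−1.96 − b/0.309).

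| Assumed shift per interviewed mother | Whole arm interviewed first | Half the arm interviewed first |
|---|---|---|
| 0.1 SD | 6.2% | 5.3% |
| 0.2 SD | 9.9% | 6.2% |
| 0.3 SD | 16.3% | 7.7% |

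The half-arm column uses b equal to half the assumed shift. The formula is symmetric, so a downward shift of the same size gives the same figures.

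**The case against.** The strongest reply is that order within a timepoint is the sort of detail an article leaves to the full protocol, which is not shown and may well set it. The interviews are also described as adding context to the quantitative data, which suggests a follow-up role. Part of this stands: a rule may exist elsewhere. But the article does more than stay silent. It prints interview windows that permit the interview first, and it restricts interviews to one arm.

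A second reply is that the suggested order can make one contrast worse. Both scales are measured only at 6 and 12 months. With the questionnaire first, the midpoint interview falls between the two measurements, and any lasting effect goes wholly into the change. Under the current windows some of it might cancel. This limits the remedy and should be said openly. It does not defeat it, because the midpoint interview precedes the 12-month form under either schedule, and cancellation between unknown quantities is not a safeguard.

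Third, the analyses are mostly exploratory, one-arm interviews are common in pilots, and the Limitations section already accepts that the groups may not be comparable. That is fair, and it keeps the importance moderate.

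Some stronger readings are tempting but unsupported:

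- A reader might infer that three quarters of mothers at midpoint (1.5 of 2 months) and half at endpoint (1 of 2 months) are interviewed first. Those are shares of window length, measured against questionnaires at exactly 6.0 and 12.0 months. The article says only midpoint, endpoint and around 6 months, so the questionnaires may fall anywhere in the same windows.
- A reader might infer that the interview breaks the stated blinding, "Participants are blind to whether they receive Standard Family Spirit or Precision Family Spirit as randomization occurs at the site-level". The interview guide is not shown, so nothing establishes that it discloses the tailoring or the allocation.
- A reader might extend the point to the Working Alliance Inventory. The stated interview topics are acceptability and satisfaction only.

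**Conclusion.** The point holds as a weakness in the stated schedule. The plan permits, in one arm only, a study interview on two primary constructs shortly before those constructs are scored, and the analysis cannot separate its effect from that of the strategy.

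It is not shown that a shift occurs, that it favours Precision, or how large it is. The rejection rates above rest on an assumed 0.1 to 0.3 SD, 21 mothers per arm, a two-sided test and no clustering, and they serve for scale only. How many mothers are exposed depends on uptake by invitation and on questionnaire dates, neither of which is given. The point should be addressed because the remedy is mainly a matter of scheduling, but it does not threaten the pilot as a whole.

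**What to change.** - At each timepoint, hold the interview only after that mother has completed her acceptability and satisfaction forms. Where a form is not returned, hold it after the form's window has closed, so that non-responders can still be interviewed. This requires a stated questionnaire window and a matching adjustment of the interview windows.
- Record the date of each form and each interview.
- Add a sensitivity analysis that flags Precision mothers interviewed before their questionnaire at the same timepoint, including any already interviewed. The first consent was in June 2019, so some may have been.
- State as a limitation that the midpoint interview still precedes the 12-month questionnaire in one arm, so carry-over into the 6-to-12-month change is not removed.

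The cost is small. Interviews fall slightly later, a few may be missed, and a minor amendment to the review board is needed. No Standard-arm interviews are required, and the order suits the interviews' stated purpose of adding context to the questionnaire data.
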